#### **3.3.3 Case Report Forms**

[figure not shown]

All information will be recorded by the investigator or a designated person in the Case Report Forms. Case Report Forms will be completed with a black ball-point pen and signed by the investigator. For every vaccination a new section of CRF will be used. They will be labelled CRFA, CRFB, CRFC and CRFD.

Where applicable, intensity/severity data in the CRF will be collected according to a continuous scale. Only upon evaluation of the data will the intensity be categorised into mild/moderate/severe, according to the severity scales (appendix 3).

Explanations must be given for all missing information. All incorrect data must be crossed out with a single line, then signed and dated by the investigator (except date corrections). "White-out" correction fluid must not be used.

### **3.4 Procedures for Obtaining, Handling and Shipment of Biological Samples**

#### **3.4.1 Trial Laboratories**

The biological safety parameters will be measured on serum samples at the UMCN of Nijmegen

The immunological assessment will be performed at the UMCN in Nijmegen under [name] supervision and at BPRC under [name] supervision

#### **3.4.2 Obtaining Serum Samples and blood cells**

Per visit, a maximum of 40 mL of blood will be collected in vacutainer tubes at visits V1, V2, V5, V7, V10, V11, V13, V13, V18 and V19 by the nurse in charge of vaccination. Immediately prior to blood sampling, the person in charge of the procedure should verify subject's identity and should check that the initials on the laboratory request form are those of the subject. Then, the subject's initials must be recorded on all labels of the corresponding band. One label will be affixed onto the vacutainer tube immediately prior to blood sample drawing.

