## FLOW CHART

**Prime & Boost phase, 19 Visits, 3 Vaccinations, Randomised, Dose Escalating, 365 Days duration/subject**

| Visit Number                    | V1                                          | V2              | V3               | V4         | V5         | V6              | V7               | V8            | V9         | V10        | V11             | V12               | V13                  | V14            | V15         | V16         | V17             | V18              | V19           |
|---------------------------------|---------------------------------------------|-----------------|------------------|------------|------------|-----------------|------------------|---------------|------------|------------|-----------------|-------------------|----------------------|----------------|-------------|-------------|-----------------|------------------|---------------|
| Trial Timelines (Days,)         | D-28                                        | D0              | D1               | D3         | D7         | D14             | D28              | D29           | D31        | D35        | D42             | D56               | D112                 | D113           | D115        | D119        | D126            | D140             | D365          |
| Time Windows (Days or Hours)    |                                             | ± 7 D           | ± 6 hrs          | ± 24 hrs   | ± 24 hrs   | ± 2 D           | ± 2 D            | ± 6 hrs       | ± 24hrs    | ± 24 hrs   | ± 2 D           | ± 2 D             | ±7 D                 | ± 6 hrs        | ± 24hrs     | ± 24 hrs    | ± 2 D           | ± 2D             | ± 14 D        |
| Visit Intervals                 |                                             | V1
+4
wks | V2
+24
hrs | V2
+ 3D | V2
+ 7D | V2
+2
wks | V4
+ 2
wks | V7
+ 24hrs | V7
+ 3D | V7
+ 7D | V7
+2
wks | V11
+ 2
wks | V7
+12wks         | V13
+ 24hrs | V13
+ 3D | V13
+ 7D | V9
+2
wks | V11
+2
wks | V1
+1 year |
| Vaccination Doses               |                                             | Vac1     |                  |            |            |                 | Vac2      |               |            |            |                 |                   | Vac3          |                |             |             |                 |                  |               |

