| Prior and concomitant therapy   |                                             | X               |                  |            |            |                 | X                |               |            |            |                 |                   | X                    |                |             |             |                 |                  |               |
| Blood Sampling                  | BS1                                         | BS2             |                  |            | BS3        |                 | BS4              |               |            | BS5        |                 | BS6               | BS7                  |                |             | BS8         |                 | BS9              | BS10          |
| AMA-1 IgG, IgG isotypes, IgM    |                                             | X               |                  |            |            |                 | X                |               |            |            |                 | X                 | X                    |                |             |             |                 | X                | X             |
| GIA; t-cell proliferation       |                                             | X               |                  |            |            |                 |                  |               |            |            |                 | X                 |                      |                |             |             |                 | X                |               |
| IFN $\gamma$ , ELISPOT          |                                             | X               |                  |            |            |                 |                  |               |            |            |                 |                   | X                    |                |             |             |                 | X                | X             |
| Trial Phase                     | Primary Immunisation                        |                 |                  |            |            |                 |                  |               |            |            |                 |                   | Booster Immunisation |                |             |             |                 |                  |               |

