### 3.2.2 Vaccination, Clinical Follow-up and Serology schedule

The vaccination and serology schedule is summarized in the flow chart (see page 9). Each subject will attend at 13 standardised visits at the trial centre (Inclusion visit D-28; D0; D1; D14; D28; D29; D42; D56; D112; D113; D126; D140; D365). Two doses of vaccine at 4 week-interval will be given by intra-muscular route at D0 and D28. A booster dose will be given 12 weeks after the primary series at D112.

Blood samples will be taken at ten time points at D-28; D0; D7, D28; D35, D56; D112; D119, D140, and D365. Before each vaccination and 7 and 28 days after each vaccination a venapuncture will be performed. Biological parameters are assessed at inclusion, 7 and 28 days after each vaccination and after a year. Blood for immunologic assays will be collected at inclusion, before each vaccination, 28 days after each vaccination and a year after the first immunisation. A venapuncture will be performed ten times during the course of the study. A maximum total of 40 mL blood will be taken at each blood sampling. For each subject a maximum of 400 mL blood will be taken during the whole study.

Twenty four hours, 3 days, 7 days and 14 days after each vaccination a visit is planned to monitor adverse events at D1, D3, D7, ,D14, D29, D31, D35, D42, D113, D114, D119 and D126.

[figure not shown]

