**Checklist for phone callers:**

- ☐ 1. Between 18 and 45 years old
- ☐ 2. Available for screening
- ☐ 3. Available for study
- ☐ 4. Within 30 min traveling to hospital, reachable by phone
- ☐ 5. Not pregnant, not lactating
- ☐ 6. Prepared to take pregnancy test
- ☐ 7. Prepared to undergo HIV test
- ☐ 8. Prepared to visit hospital 13 times
- ☐ 9. No chronic illness, good general health
- ☐ 10. No medication or drug use
- ☐ 11. Has not been in malaria-endemic area for past 6 months
- ☐ 12. No history of malaria infection or malaria vaccine study
- ☐ 13. Not enrolled in other trial

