**Checklist day 0:**

- ☐ 1. Malaria background
- ☐ 2. 3 vaccinations
- ☐ 3. Possible side-effects
- ☐ 4. Pregnancy tests
- ☐ 5. 13 visits
- ☐ 6. 7 blood samples
- ☐ 7. Physical examinations
- ☐ 8. Insurance
- ☐ 9. Privacy
- ☐ 10. Payment for participation
- ☐ 11. Blood donor / pregnancy / travels abroad

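### Section 3.4.2 draws blood at D42 instead of D56 and omits D119, against the ten draw days in 3.2.2 and the flow chart; other visit lists in the protocol conflict as well

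*Protocol*

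**What the plan says.** Section 3.2.2 of the protocol fixes the draw days: "Blood samples will be taken at ten time points at D-28; D0; D7, D28; D35, D56; D112; D119, D140, and D365". The flow chart is titled "Prime & Boost phase, 19 Visits, 3 Vaccinations". Its row "Blood Sampling" places BS1 to BS10 at V1, V2, V5, V7, V10, V12, V13, V16, V18 and V19.

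Section 3.4.2, the instruction for the draw itself, says that blood is collected "at visits V1, V2, V5, V7, V10, V11, V13, V13, V18 and V19 by the nurse in charge of vaccination".

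Section 3.2.2 also says "Each subject will attend at 13 standardised visits at the trial centre" and names the days: "Inclusion visit D-28; D0; D1; D14; D28; D29; D42; D56; D112; D113; D126; D140; D365". The same section then plans adverse-event visits on further days, including D7, D35 and D119. In Appendix 8 the telephone checklist has "Prepared to visit hospital 13 times". The day-0 checklist also has 13 visits, with "7 blood samples".

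The flow chart's interval row times V19 as V1 plus one year, under a column headed D365. Section 7.4.3 makes the number and spacing of blood samples a per-protocol criterion and gives a further visit list: it includes V11 and V12, leaves out V13, and calls V9 the D112 sample.

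**The concern.** A visit list for blood draws is an operational rule, and a sample not drawn on its day cannot be recovered.

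D56 is the one-month post-dose-2 point for biological safety, which is part of the primary criterion (7.1.1). It also serves IgG (7.2.1), T-cell proliferation and ELISPOT (7.2.2), and the seven exploratory assays (7.3): ten assays by the text of section 7. D119 is the day-7 safety laboratory sample after the booster.

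The day-7 draws also feed the safety review. Section 6.2.3 requires out-of-range laboratory values to reach the Safety Monitor by Day 19 after vaccination, and the day-7 draw is the only one planned between a dose and that date. On the 13-visit list, the reviews after doses 1 and 2 would have no post-dose laboratory data.

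V19 supplies the persistence measurement, which 3.1.1 uses in choosing the dosage.

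**Working it through.** **Step 1: map visits to days.** From the flow chart header: V1 = D-28, V2 = D0, V4 = D3, V5 = D7, V7 = D28, V9 = D31, V10 = D35, V11 = D42, V12 = D56, V13 = D112, V16 = D119, V18 = D140, V19 = D365.

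**Step 2: compare the draw lists with the ten days of 3.2.2.**

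| Source | Days | Missing | Extra |
|---|---|---|---|
| Flow chart | D-28, D0, D7, D28, D35, D56, D112, D119, D140, D365 | none | none |
| 3.4.2 | D-28, D0, D7, D28, D35, D42, D112, D112, D140, D365 | D56, D119 | D42; D112 twice |
| 7.4.3, main list | D-28, D0, D7, D28, D35, D42, D56, D119, D140, D365 | D112 (given to V9, which is D31) | D42 |

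The flow chart reproduces 3.2.2 exactly. Section 3.4.2 has nine distinct draws. Its D42 draw is 56 - 42 = 14 days early for the post-dose-2 sample.

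**Step 3: compare the visit lists.** The flow chart has 19 visits and the list in 3.2.2 has 13. The six absent days are D3, D7, D31, D35, D115 and D119. Three of them (D7, D35, D119) are draw days: 3 x 60 = 180 samples without a visit on that list. Removing them leaves 10 - 3 = 7 draws, which matches the day-0 checklist and the seven days of the synopsis serology schedule. The adverse-event list in 3.2.2 restores D7, D35 and D119, but gives D114 where the flow chart has D115 (112 + 3 = 115).

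**Step 4: V19.** V1 plus one year is -28 + 365 = D337. With the 14-day window this is D323 to D351, against D351 to D379 around D365. The two windows meet only at D351.

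**Step 5: test for an older numbering.** Number the 13 days of 3.2.2 in order: V4 = D14, V5 = D28, V7 = D42, V9 = D112, V11 = D126.

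- Diary collection in 3.3.2 (V4, V7, V11) is then D14, D42 and D126, which is 14 days after each dose. On current numbering it is D3, D28 and D42.
- The interval in 7.4.3 for dose 3 (V5 + 12 weeks) is 28 + 84 = D112. On current numbering it is 7 + 84 = D91.
- V9 as the D112 sample in 7.4.3 fits.
- In the flow chart's interval row, V7 = V4 + 2 weeks gives D28, V17 = V9 + 2 weeks gives D126, and V18 = V11 + 2 weeks gives D140. On current numbering these give D17, D45 and D56.

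Most of the discrepancies are explained this way. The V11 and second V13 in 3.4.2 are not, and look like slips for V12 and V16. The V19 interval is not explained either, since V1 is D-28 in both numberings.

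**Step 6: per-protocol intervals in 7.4.3.** Samples are to be 4 weeks (± 2 days, so 26 to 30 days) after the preceding sample. With ten draws, D7 to D28, D35 to D56 and D119 to D140 are each 21 days. The D112 sample is to be 12 weeks (± 7 days, so 77 to 91 days) after the preceding one, but 112 - 56 = 56 days. A subject seen exactly on schedule fails.

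**Step 7: ELISPOT.** The flow chart marks D0, D112, D140 and D365. Section 7.2.2 says D0, D56 and D140.

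**The case against.** The best defence is that the intended schedule is not in doubt. The ten-day list and the flow chart's sampling row agree. Section 3.2.2 also states the rule behind them: a draw before each vaccination and at 7 and 28 days after it. The assay sections repeat D56, and a ten-entry list with V13 twice is visibly wrong. Staff working from the sampling row would lose nothing. This stands, and it makes the losses conditional. They also come from different texts: 3.4.2 keeps D7 and D35, while the 13-visit list keeps D56. No single text loses all of these samples.

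The defence is weaker than it looks in two respects. The flow chart carries errors in its own interval row. And V11 appears as a blood-sample visit in both 3.4.2 and 7.4.3.

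A reader might infer more than the protocol supports:

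- That volunteers consent to fewer visits and samples than they undergo. The consent form is not among the pages available; only the checklists conflict.
- That the macaque results show a D42 sample would change the adjuvant picture. The D42 ratio of AS02A to Alhydrogel (0.52, 95% CI 0.25 to 1.06) was not significant, no D56 value is given, and this trial makes no between-group comparison.
- That a 28-day shift of V19 implies a known change in antibody level. That needs a half-life, which the protocol does not give.

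**Conclusion.** The contradiction is established by reading alone and should be removed before the first subject is vaccinated.

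If 3.4.2 is followed, 60 of 60 post-dose-2 samples are drawn 14 days early and 60 of 60 D119 samples are missed. If the 13-visit list is followed, up to 180 day-7 samples have no visit. These are worst cases on separate assumptions about which text governs. They should not be added together or read as expected losses.

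The ten-assay count at D56 takes ELISPOT from 7.2.2; by the flow chart it is nine. The checklists understate the flow chart by 6 visits and 3 draws.

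The per-protocol definition fails whichever draw list is used. With the 3.4.2 draws, no subject has the D56 and D119 samples; with the ten-draw schedule, the stated intervals cannot be kept by a subject on time. The primary analysis is not affected through this route, because 7.4.3 bases it on all subjects with at least one dose.

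**What to change.** Make one text amendment:

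- **3.4.2:** list V1, V2, V5, V7, V10, V12, V13, V16, V18 and V19.
- **3.2.2:** replace the 13-visit list with the 19 flow-chart visits, and reconcile D114 with D115.
- **Flow chart, interval row:** correct V7, V17, V18 and V19 so that each gives the day in its own column header.
- **7.4.3:** align visit numbers, sample list and intervals with the ten draws. Remove V11, restore V13, correct the V9 label, restate the 4-week and 12-week gaps between samples, and reconcile the V5 reference for dose 3 with the flow chart.
- **3.3.2:** correct the diary-collection visits to those 14 days after each dose. The flow chart as read here collects the third diary at V16 (D119), so check that cell too.
- **7.2.2 and flow chart:** reconcile the ELISPOT days (D56 or D112, and whether D365 is included).
- **Appendix 8:** state 19 visits in both checklists and 10 samples in the day-0 checklist. Check that the volunteer information agrees.

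The cost is the amendment itself. No visit, draw or subject is added beyond the flow chart. The heavier burden now stated to callers may cost a few enrolments.

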#### **3.4.3 Handling Serum Samples**

##### ***Aliquoting for Immunological tests***

Aliquoting must be performed subject by subject to avoid mixing blood tubes. The following procedure must be followed:

1. After centrifugation, the person responsible for aliquoting should carry out the operation by taking the tubes one by one from the centrifuge.
2. The operator will only place in a rack five Sarstedt tubes necessary for aliquoting and will affix the completed labels onto the tubes.
3. Aliquoting will be performed according to the required volume of 1.8 mL, the number of tubes, and the priority of titrations.
4. Pre-labelled Sarstedt tubes that would not have been filled for lack of serum will be removed.
5. The subject's identification number and initials, the date of sampling, the number of aliquots obtained, and the date and time of aliquoting will be specified on the sample identification list. A label will be affixed onto the three sheets of the list. If the date is included on the vial, the technician will not be blinded for vaccine dose!
6. Comments may be made on the quality of samples (haemolysed, contaminated, etc.).
7. The next sample will be taken out of the centrifuge only when the steps 1 through 6 are completed.

##### ***Storage Conditions***

[figure not shown]

Each aliquot must be frozen at -80°C. The temperature must be monitored and documented on the appropriate form (see operating guidelines) during the entire trial.

## **4 SELECTION AND WITHDRAWAL OF SUBJECTS**

### **4.1 Inclusion Criteria**

- Age > 18 and < 45 years healthy volunteers (males or females).
- General good health based on history and clinical examination.
- All volunteers have to sign the informed consent form.
- Negative pregnancy test.
- Use of adequate contraception for females up to three months after the third injection (D140).
- Reachable by phone during the whole study period (18 months).

### **4.2 Non-Inclusion Criteria**

- History of malaria or residence in malaria endemic areas within the past six months.
- Positive serology for malaria antigen PfAMA-1
- Previously participated in any malaria vaccine study
- Symptoms, physical signs and laboratory values suggestive of systemic disorders, including renal, hepatic, cardiovascular, pulmonary, skin, immunodeficiency, psychiatric and other conditions, which could interfere with the interpretation of the study results or compromise the health of the volunteers.
- Any laboratory abnormalities on screened blood samples beyond the normal range, as defined at UMC St Radboud. Positive HIV, HBV or HCV tests.
- Volunteers should not be enrolled in any other clinical trial during the whole trial period.
- Volunteers should not receive chronic medication, especially immunosuppressive agents (steroids, immunomodulating or immunosuppressive drugs) during the three months preceding the screening visit or during the study period.
- Pregnant or lactating women.
- Volunteers unable to give written informed consent.
- Volunteers unable to be closely followed for social, geographic or psychological reasons.
- Previous history of drug or alcohol abuse interfering with normal social function during a period of one year prior to enrolment in the study.
- Volunteers should not perform exercise four hours before blood draw and should not donate blood for non study-related purposes during the entire duration of the study.
- Known hypersensitivity to any of the vaccine components (adjuvant or peptide).
- Volunteers are not allowed to receive any vaccination or gammaglobuline during a period three months prior to the first immunisation and up to six months after the 3rd immunisation. If a vaccination is necessary during this period, the volunteer will be withdrawn from the study.
- Volunteers are not allowed to travel to malaria endemic countries during the study period.

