### **4.3 Conditions for Withdrawal from further Vaccination**

1. Any serious adverse reaction as defined in section 7.1
2. Any adverse event that, according to clinical judgement of the investigator, is considered as a definite contra-indication to proceeding with the vaccinations. The holding procedure will then apply, please refer to section 6.2.2

[figure not shown]

3. The use of concomitant, chronic medication active on the immune system (steroids, immunosuppressive agents)
4. Other vaccinations received during the first 140 days of the study
5. Pregnancy

In case of intercurrent disease such as hay fever episode, flu-like syndrome, upper respiratory disease, considered as mild and expected to be promptly resolved, the vaccination could be postponed for no more than 7 days.

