#### **4.4 Conditions for Withdrawal from the Trial**

Volunteers will be completely withdrawn from the trial under the following conditions:

1. Free decision by the volunteer
2. Death
3. Completely lost to follow-up

Volunteers wishing to interrupt their participation in the study before the second vaccination will be replaced. There is a premature withdrawal from the study when a volunteer stops participation before the second immunisation whatever the circumstances. If a volunteer withdraws it has to be checked that this is due to circumstances not related to the trial. If a volunteer withdraws due to adverse events, the volunteer should not be replaced.

If a subject fails to appear for a follow-up examination, extensive effort (i.e., documented phone calls and certified mail, *to be adapted to trial setting*) should be undertaken to locate or recall him/her or at least to determine his/her health status. These efforts should be documented in the subject's CRF and source documents.

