### 5.3 Prior and Concomitant Therapy

Immunosuppressive or immunomodulator treatments are an exclusion criteria. If any volunteer will need chronic use of one of these medicine, the subject will be excluded from further vaccination. Furthermore, any data obtained after initiating this medication will be considered deviating.

Antipyretic or painkiller will not be allowed as preventive treatment of pain or fever, before the immunisation.

Other vaccinations will not be allowed during a three-month period before the first trial vaccine injection and within the six-month period after the third trial vaccine injection. If a vaccination is necessary during the banning time window, data collected from these subjects will be considered as deviation to the protocol.

For all other treatment, the following data will be specified and recorded on case report forms:

- Trade name and generic name (as many prescription drugs in the Netherlands are generic)
- Total daily dose
- Start and stop dates (and, if appropriate, timing requirements within the day: AM, PM, post-shot)
- Indication

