### **6.3.3 Time period, frequency, and method of detecting adverse events and serious adverse events**

All AEs occurring within one month following administration of each dose of vaccine must be recorded on the Adverse Event form in the subject's CRF, irrespective of severity or whether or not they are considered vaccination-related.

The standard time period for collecting and recording SAEs will begin at randomization or the first receipt of vaccine and will end one month following administration of the last dose of study vaccine for each subject. See Section 6.3.4 for instructions for reporting and recording SAEs.

Additionally, in order to fulfil international reporting obligations, SAEs that are related to study participation (e.g. procedures, invasive tests, a change from existing therapy) or are related to a concurrent medication will be collected and recorded from the time the subject consents to participate in the study until she/he is discharged.

The investigator will inquire about the occurrence of AEs/SAEs at every visit/contact during the study and throughout the follow-up phase as appropriate.

All AEs either observed by the investigator or one of his clinical collaborators or reported by the subject spontaneously or in response to a direct question will be evaluated by the investigator. AEs not previously documented in the study will be recorded in the Adverse Event form within the subject's CRF. The nature of each event, date and time (where appropriate) of onset, outcome, intensity and relationship to vaccination should be established. Details of any corrective treatment should be recorded on the appropriate page of the CRF.

As a consistent method of soliciting AEs, the subject should be asked a non-leading question such as:

"Have you felt different in any way since receiving the vaccine or since the previous visit?"

AEs already documented in the CRF, i.e. at a previous assessment, and designated as "not recovered/not resolved" or "recovering/resolving" should be reviewed at subsequent visits, as necessary. If these have resolved, the documentation in the CRF should be completed.

N.B. If an AE changes in frequency or intensity during the specified reporting period, a new record of the event will be entered.

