#### **6.5.4 Post study adverse events and serious adverse events**

A post-study AE/SAE is defined as any event that occurs outside of the AE/SAE detection period defined in Section 6.3.3. Investigators are not obligated to actively seek AEs or SAEs in former study participants.

However, if the investigator learns of any SAE, including a death, at any time after a subject has been discharged from the study, and he/she considers the event reasonably related to the investigational product, the investigator will promptly notify the Study Contact for Reporting SAEs.

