#### **6.6 Pregnancy**

Subjects who become pregnant during the study (one month after the first dose or three months after the second dose) must not receive additional doses of study vaccine but may continue other study procedures at the discretion of the investigator.

The investigator, or his/her designee, will collect pregnancy information on any subject who becomes pregnant while participating in this study. The investigator, or his/her designee, will record pregnancy information on the Pregnancy Report Form and submit it to EMVI and GSK within 24 hours of learning of a subject's pregnancy, regardless of the adjuvant used. The investigator will inform the safety monitor as soon as possible. The safety monitor will break the code for the pregnant subject and inform GSK and EMVI about the adjuvant used. The investigator will remain to be blinded.

The subject will be followed to determine the outcome of the pregnancy. At the end of the pregnancy, whether that be full-term or prematurely, information on the status of the mother and child will be forwarded to EMVI and GSK. Generally, follow-up will be no longer than six to eight weeks following the estimated delivery date.

While pregnancy itself is not considered an AE or SAE, any pregnancy complication or elective termination of a pregnancy for medical reasons will be recorded as an AE or a SAE, as described in Section 6.3 and 6.4, and will be followed as described in Section 6.5.

A spontaneous abortion is always considered to be a SAE and will be reported as described in Section 6.5. Furthermore, any SAE occurring as a result of a post-study pregnancy AND considered reasonably related in time to receipt of the investigational product by the investigator, will be reported to EMVI and GSK Biologicals as described in Section 6.5.4. While the investigator is not obligated to actively seek this information from former study participants, he/she may learn of a pregnancy through spontaneous reporting.

Information on pregnancies identified during the screening phase/prior to vaccine administration does not need to be collected; this information need not be communicated to safety.

[figure not shown]

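### Section 4.2 and the synopsis withdraw a volunteer from the study for an outside vaccination, while 4.3, 4.4 and 5.3 do not; applied to a dosed volunteer, 4.2 would end the scheduled safety visits

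*Protocol*

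**What the plan says.** Five places in the protocol bear on a volunteer who needs a vaccination outside the trial.

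- **Section 4.2 and synopsis item 14** ban any vaccination or gammaglobuline from three months before dose 1 to six months after dose 3, and continue: "If a vaccination is necessary during this period, the volunteer will be withdrawn from the study".
- **Section 4.3**, which lists reasons to stop giving trial vaccine, has as item 4: "Other vaccinations received during the first 140 days of the study".
- **Section 4.4** opens "Volunteers will be completely withdrawn from the trial under the following conditions" and lists three: the volunteer's free decision, death, and complete loss to follow-up. Outside vaccination is not among them.
- **Section 5.3** repeats the three-month and six-month window and says: "If a vaccination is necessary during the banning time window, data collected from these subjects will be considered as deviation to the protocol". It does not mention withdrawal.
- **Section 6.6**, for comparison, says that a subject who becomes pregnant "must not receive additional doses of study vaccine but may continue other study procedures at the discretion of the investigator".

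The follow-up at stake is set in 3.2.2 ("Biological parameters are assessed at inclusion, 7 and 28 days after each vaccination and after a year"), in the flow chart, and in 6.3.3 ("All AEs occurring within one month following administration of each dose of vaccine must be recorded on the Adverse Event form"). For people who have left the study, 6.5.4 adds: "Investigators are not obligated to actively seek AEs or SAEs in former study participants".

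**The concern.** One event carries different consequences depending on the section consulted, and no order of precedence is given. The rule in 4.2 cannot be read as a screening rule only, because its window runs well past the third dose and so covers people who have had one, two or three doses. Withdrawal is right for a screened volunteer who has not been dosed. For a dosed volunteer it takes away the scheduled observation of doses already given.

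Safety is the primary objective, each group has 10 subjects, and the primary analysis in 7.4.3 keeps everyone with at least one dose. One dosed subject without follow-up is therefore 1/10 = 10% of a group. The holding rule in 6.2.2 also counts Grade 3 events per 10 subjects over the 14 days after vaccination, so a subject withdrawn in that period may go unobserved for it.

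**Working it through.** No sample size, power or error rate is involved. The check has two parts: where the rules overlap in time, and what a dosed volunteer would lose if 4.2 were applied.

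**Overlap of the rules**

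Inputs: doses at D0, D28 and D112 (2.1); the window in 4.2; the 140-day limit in 4.3 item 4.

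- End of the 4.2 window, taking six calendar months as 181 to 184 days: D112 + 181 = D293 to D112 + 184 = D296.
- D0 to D140: 4.2 says out of the study, 4.3 says no more trial doses. The two differ.
- D140 to about D293–D296: 4.3 is silent, but 4.2 still differs from 4.4 and 5.3.
- The last dose is at D112, so 4.3 item 4 can withhold a dose only before D112. After dose 3 the only effect of 4.2 is to remove observation.

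**What would be lost**

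Inputs: the 19 visits and their days in the flow chart, the blood schedule in 3.2.2, and the one-month recording rule in 6.3.3. Only visits that serve doses already given are counted. In the D29 case V13 to V18 are left out, because they are tied mainly to a third dose that 4.3 would cancel anyway.

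| | Withdrawn D29 (V8), day after dose 2 | Withdrawn D113 (V14), day after dose 3 | Withdrawn after D140 (V18) |
|---|---|---|---|
| Visits lost | V9 (D31), V10 (D35), V11 (D42), V12 (D56), V19 (D365) = 5 of 19 | V15 (D115), V16 (D119), V17 (D126), V18 (D140), V19 (D365) = 5 of 19 | V19 = 1 of 19 |
| Reactogenicity visits lost, of the four at 24 hours and days 3, 7 and 14 | D31, D35, D42 = 3 of 4 | D115, D119, D126 = 3 of 4 | none |
| Reactogenicity days not covered | D42 − D29 = 13 of 14 | D126 − D113 = 13 of 14 | none |
| Scheduled safety bloods lost | D35, D56, D365 | D119, D140, D365 | D365 |
| Of these, in the primary biological criterion of 7.1.1 (one month after each dose) | D56 | D140 | none |

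Three notes on the counts:

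- The 14 days are counted as days 1 to 14 after the dose. Section 6.2.3 counts the vaccination day as the first of the 14, which gives D41 − D29 = 12 and D125 − D113 = 12.
- Withdrawal on the dosing day itself would add the 24-hour visit, making 6. The examples are therefore near the worst case and not exactly at it.
- Section 3.2.2 lists 13 standardised visits before adding the day-3 and day-7 visits. On that shorter list each example loses 3 of 13 (D42, D56, D365 or D126, D140, D365).

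**Adverse event recording at risk**

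Taking one month as 28 to 31 days, the period after dose 2 ends at D56 to D59, and D56 − 29 = 27 to D59 − 29 = 30 days remain. After dose 3 it ends at D140 to D143, and 140 − 113 = 27 to 143 − 113 = 30 days remain. Section 6.3.3 makes no exception for withdrawn subjects, so these days are at risk and not plainly lost.

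**The case against.** The other side has four good points.

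**The sections on withdrawal already agree.** Section 4.2 is an eligibility list. Section 4.3 stops doses only, 4.4 does not list the event, and 5.3 speaks of data collected from these subjects, which fits their staying in. Read together, these give the sensible outcome, and the harm needs staff to follow the eligibility bullet instead. That is fair, and it makes the consequence conditional. But 4.2 and the synopsis state their rule without condition, and 4.5 recognises discontinuation by the investigator, so the 4.4 list may not be exhaustive. The conflict with 4.3 and 5.3 does not depend on 4.4.

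**Adverse event recording may survive.** A reader might infer from 6.5.4 that all event detection ends on withdrawal. The documents do not support that. Section 6.5.4 concerns events outside the detection period of 6.3.3, and both examples begin inside it. Section 6.3.3 requires recording for one month after each dose. Section 6.4 continues follow-up of an SAE already present or of a subject withdrawn because of an adverse event, and 6.5.4 keeps related SAEs reportable if the investigator learns of them. What 4.2 clearly removes is the scheduled visits and bloods, which are the practical means of finding new events.

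**Not all the bloods bear on the primary criterion.** A reader might count three primary safety samples lost per example. Only the one-month sample belongs to the biological criterion in 7.1.1. The day-7 and one-year samples are scheduled but fall outside it.

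**The event may be rare, and the pregnancy comparison is limited.** Volunteers accept a vaccination ban and may not travel to malaria-endemic countries, and the documents give no frequency. Section 6.6 lets procedures continue only at the investigator's discretion. It shows that stopping doses need not mean leaving the study, but it does not guarantee follow-up.

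**Conclusion.** The contradiction stands: 4.2 and the synopsis prescribe withdrawal from the study for an event that 4.3 and 5.3 handle without it and that 4.4 does not list. If 4.2 is applied to a dosed volunteer, the loss is 5 of 19 visits in the two near-worst cases, including three of four reactogenicity visits and the one-month safety blood, and 1 of 19 after D140. This rests on the flow chart's visit days, on withdrawal meaning no further scheduled visits, and on leaving out visits tied to a cancelled dose 3. Loss of adverse event recording within a month of a dose is possible but not established, given 6.3.3.

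The number of subjects affected cannot be derived from the documents. The primary analysis set is unchanged, because data before withdrawal stay in and 7.4.3 already covers every dosed subject. A reader might infer that the 140-day limit in 4.3 item 4 must be lengthened to match the six months in 4.2. It need not be, because no dose is due after D112. The change should be made: the trial exists to observe safety in small groups, and it costs little.

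**What to change.** In 4.2 and synopsis item 14, keep exclusion for volunteers not yet dosed. For volunteers who have received at least one dose, replace the withdrawal sentence with:

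> will receive no further trial doses but will remain in scheduled safety visits and SAE follow-up to D365 (as in 7.1.1); the date of the outside vaccine or gammaglobuline is recorded and later data are marked as deviating (5.3).

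Two points on the wording. For SAE follow-up it takes the period in 7.1.1, which runs throughout the study, whereas 6.3.3 generally ends SAE collection one month after the last dose. It also limits the deviation mark to data after the outside product, as 5.3 already does for immunosuppressive medication.

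The cost is protocol wording only. The downside is a few safety records confounded by another vaccine, which can be identified from the recorded date.
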